## Abstract

Dental caries is a major oral disease resulting from a complex interaction between the commensal microbiota, host susceptibility (heredity, immunity, diseases, etc.) and environmental factors (diet, dental hygiene, etc.). To predict the patient's risk of new carious lesions or progression of existing lesions, the Caries Risk Assessment (CRA) takes account of clinical, biological and behavioural factors. Thus, the CRA can predict whether the patient is at high or low risk of developing caries. The practitioner can thus set up a follow-up adapted to the risk of the patient. However, although bacteria are the main etiological factor of carious lesions, the CRA does not consider bacterial quantification or just focus on the level of *S. mutans* in the saliva. As the majority of cavities are interproximal in adolescence, the aim of this trial is to identify and quantify the interdental microbiota of adolescents aged from 15 to 17 years with low or high carious risk. So, the quantification of new biomarkers associated with carious lesion could be added to the CRA to improve it.

## Introduction

1

Caries is a major oral clinical disorder induced by a compound of microbiota whose composition varies continuously depending on the chemistry and environment of the dental site but also other more general factors such as saliva [1]. The main determinant of the evolution of the biofilm at a particular tooth site is its environment and whether the severity level of the disorder is such that it would lead to demineralization and visible changes at the site [1]. Although caries are clearly bacterial diseases, they are not infectious diseases in the classical sense because they result from a complex interaction between the commensal microbiota, host susceptibility (heredity, immunity, diseases …) and environmental factors (diet, dental hygiene …) [2].

The risk factors for caries are clinical, biological and behavioural. They predict the patient's risk of new carious lesions or progression of existing lesions [3]. By analysing all the risk and protective factors for a patient's carious disease, the clinician can assess the patient's risk for the future. This analysis procedure is called a Caries Risk Assessment (CRA) [1]. If there is an increasing interest in incorporating CRA into routine, the determining factors of caries disease are mainly dental practice, age, gender, ethnicity, oral hygiene habits, diet, education and socio-economic status [4].

The CRA for children and adolescents doesn't consider bacterial quantification, a factor highly linked to the development of caries [5]. In fact, the main factor initiating dental decay is the oral microbial dysbiosis [6]. During the carious process, the composition of the microbiota evolves. In the absence of carious lesion, the microbiota of dental enamel is principally composed of non-mutans *streptococcal* and *actinomyces* bacteria*.* Aciduric bacteria, like “low-pH” non-mutans *streptococcal* bacteria, progressively accumulate. Then, acidogenic and aciduric bacteria, like *streptococcus mutans*, *lactobacillus*, *actinomyces*, and *bifidobacterium*, become dominant [6].

Moreover, depending on the location of the dental site, the risk of developing caries varies considerably [7,8], however CRA tools do not currently use this information. The majority of carious lesions in adolescents, a period during which tooth decay is still very active [9,10], are observed on the interproximal surfaces of posterior teeth due to specific anatomical, physiological, diet-related and histological considerations [11,12]. So, the analysis of the interdental microbiota of adolescents is essential for improving our understanding of the carious process factors and for providing means to facilitate caries prediction and prevention.

This trial aims to identify as well as quantify interdental microbiota in adolescents aged from 15 to 17 years. As a contribution to increase the sensitivity of CRA, the secondary outcome is to evaluate qualitatively and quantitatively the microbiota of interdental space association according to Carious Risk.

## Methods

2

### Ethics statement

2.1

The protocol and design of the study named MIARC “Microbiota of Interdental space of Adolescents according to Risk of Caries”, have been endorsed by ethical and regulatory authorities and will be carried out in conformance with the Declaration of Helsinki. The Protection of Individuals Board of South-Est VI (France) approved the protocol on November 6, 2017. The National Agency for Medical and Health Product Safety registered it on February 13, 2017 (ID-RCB ref: 2017–A00425–48). The National Commission for Information Technology and Liberties gave its approval on November 6, 2017. This study was registered with ClinicalTrials.gov (identification number NCT03700840).

All participants, their parents or legal guardians will give their informed consent before participating in the study. The consent form will be composed of the following details: name and affiliation of investigator, explanations concerning the aim readily understandable by all, the course and the duration of the study, as well as the freedom to withdraw at any time, the endorsement of the ethics committee and the guarantee of confidentiality. Each participant will receive oral assessment free of charge.

### Study design, site and population

2.2

The MIARC trial is a cross-sectional observational clinical study (Fig. 1). The cross-sectional studies guidelines set out in the statement, Strengthening the Reporting of Observational Studies in Epidemiology (STROBE), will be followed [13]. Programmed for a period of 2 months in 2019, the MIARC trial will be conducted with healthy adolescents aged 15–17 years at the Dentistry Clinic Department of the Hospital of Montpellier, France. Most of the patients belong to an urban and mainly low-income population living in or around Montpellier. However, in some cases, patients come from far away to have specific care under general anaesthetic or for non-standard dental or medical treatments.

**Fig. 1 fig1:**
[figure not shown]
Workflow of the experiment. ICDAS: International Caries Detection and Assessment System; PCR: Polymerase Chain Reaction.

Patients will be recruited during their follow-up visit in the Public Health Department of the Oral Medicine Hospital. All potential participants (Caucasian subjects aged 15–17 years) will receive a document about the study. A toll-free number will be made available for potential participants to obtain additional information should they wish. Adolescents who agree to participate will be provided with verbal and written information about the study. They will then be interviewed at the reception area of the Public Health Department. The oral examination will be conducted at the dentistry clinic to verify the individual eligibility criteria. All patients will be contacted again to schedule an appointment if they agree.

### Study population

2.3

Fifty Caucasian subjects will be selected from a group of first-time volunteers. The male/female ratio will be 1.0 as well as the CRA high risk/low risk ratio in the enrolled population.

The individual eligibility criteria are (i) aged 15-17 years-old, (ii) presence of teeth (15–16, 25–26, 35–36, and 45–46), (iii) having at least 22 natural teeth, (iv) good understanding of the French language, (v) one of the parents/legal guardians accepts the study's terms and conditions and signs the informed consent form, (vi) the adolescent accepts the terms and conditions of the study and signs the informed consent form. Moreover, the eligibility of the participant depends upon the presence of all his/her four premolar-molar pairs.

The clinical interdental site inclusion criteria are: (i) interdental brushes can penetrate into the four sites analysed, (ii) absence of diastemata, (iii) no interdental caries or prosthetics restorations in the teeth surrounding the interdental sites, (iv) absence of oral inflammation and bleeding on probing (BOP) after 30 s), (v) no clinical attachment loss (CAL) > 3 mm or pocket depth (PD) > 3 mm.

The criteria for exclusion are: (i) smokers, (ii) having an immune system disorder, (iii) having any other concomitant systemic illness, (iv) taking medication, (v) had a professional prophylaxis within the 4 weeks preceding the initial examination, (vi) taken antibiotics in the past 3 months, (vii) regularly using interdental brushes and/or dental floss and/or mouthwash, (viii) having a history of periodontal disease or treatment, (ix) undertaking a course of dental or orthodontic treatment, and (x) unable to answer questions or non-cooperative.

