#### Sample size

2.8.1

With an alpha error of 5% (2-sided test), a power of 80%, an intraclass correlation coefficient of 0.8 and a mean difference of bacteria counts between the two caries risk groups of 1,300,000, a total of 200 sites, meaning 50 subjects, needs to be selected.

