#### Analysis

2.8.2

Three main steps will be realized: preparation of descriptive summaries, modelling using a mixed (linear) model and correlating bacterial abundances. A mixed linear model for the log-count abundance of each species at a measured site will be used to test for potential effects of gender, interdental space and the location of each site. Two categorical variables (site location and gender), and one numerical variable (interdental space) will be modelled as fixed effects and one categorical variable will be modelled as a random effect (subject). This random effect will be included to model correlation between the four interdental sites of a given study participant. In the regression, each coefficient will be tested according to the null hypothesis which indicates that the coefficient is zero when a likelihood-ratio test is applied. The p-values less than 0.001, 0.05, and 0.01 will be respectively considered strong, medium and low evidence with respect to the null hypothesis. To perform the correlation analysis and avoid over-estimating the inter-site correlation, the residuals of the model described above will be used. The trees associated with the correlation plot will be generated by hierarchical cluster analysis with complete linkage. Other multivariate analyses, such as factor analysis, will be used to graphically check the correlations between bacteria quantification and all potential caries risk factors. A multilevel logistic regression analysis will finally be performed to test which oral characteristics are significantly linked with the two caries risk groups. The linear mixed effects modelling package, lme4 [21] in R environment [22] will be used to generate all statistical analyses and associated plots.

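### Sex and caries risk are each balanced 1:1 only over the whole sample, and gender is then tested without a risk-group term, so the gender coefficient can carry part of a risk effect

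*Protocol article*

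**What the plan says.** Section 2.3 (Study population) gives the sample and its balance: "Fifty Caucasian subjects will be selected from a group of first-time volunteers", and then "The male/female ratio will be 1.0 as well as the CRA high risk/low risk ratio in the enrolled population". The article describes no sex ratio within a risk group, and no matching or stratification.

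Section 2.8.2 (Analysis) specifies a mixed model for the log count of each species, "to test for potential effects of gender, interdental space and the location of each site". Its fixed effects are listed: "Two categorical variables (site location and gender), and one numerical variable (interdental space) will be modelled as fixed effects". Subject is the only random effect. Caries risk group is not in this model. It appears as the outcome of a separate multilevel logistic regression, whose explanatory variables are described only as oral characteristics. Sex is not named there.

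Section 2.8.1 (Sample size) sizes the study for the comparison of the two risk groups: "a mean difference of bacteria counts between the two caries risk groups of 1,300,000".

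**The concern.** Two separate 1:1 quotas fix the margins of the sex-by-risk table but not its cells. High-risk subjects could be mostly of one sex and low-risk subjects mostly of the other, with both ratios still exactly 1.0. Risk is assigned partly by behaviour (Table 1: brushing, snacking, dental attendance), so an association with sex is conceivable, although the documents do not report one.

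The gender test omits risk group, so a difference between risk groups can be read as a gender effect. In the other direction, a risk-group comparison without sex adjustment would carry part of any sex difference in flora. Balance at enrolment has to be fixed before recruitment; a later analysis plan can adjust for an imbalance but cannot restore the lost precision.

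**Working it through.** **Inputs from the article.** 50 subjects; both ratios 1.0, so 25 male/25 female and 25 high/25 low risk (section 2.3). Two-sided alpha 5%, power 80%, ICC 0.8, difference 1,300,000, 200 sites, i.e. 4 per subject (section 2.8.1). **Assumed:** the odds ratio between sex and risk, since none is given.

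**1. The plan's own figure.** Section 2.8.1 states "a total of 200 sites, meaning 50 subjects, needs to be selected" but gives no SD, so 50 cannot be reproduced, only inverted. The design effect is 1 + (4−1) × 0.8 = 3.4, which leaves 100/3.4 = 29.4 effective sites per group. The SD that makes 50 subjects correct is 1,300,000 / [(1.960 + 0.842) × √(2/29.4)] ≈ 1.78 million, a standardised difference of 0.73. This is used only in step 5.

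**2. Share carried over.** Let k be the number of boys in the high-risk group. The proportion at high risk is k/25 among boys and (25−k)/25 among girls. With no risk term, the gender contrast picks up the risk effect times the difference:

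share = k/25 − (25−k)/25 = (2k−25)/25.

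Site location is balanced within subject and does not alter this. The formula treats interdental space as unrelated to sex and risk. By symmetry, an unadjusted risk-group contrast picks up the same share of any sex effect.

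**3. Chance alone (sex and risk unrelated).** With both margins fixed, k follows a hypergeometric distribution (50, 25, 25).

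| Split in the high-risk group, either direction | Probability of this or worse | Share of risk effect, at least |
|---|---|---|
| 15/10 | 0.26 | 20% |
| 16/9 | 0.089 | 28% |
| 17/8 | 0.023 | 36% |

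**4. Assumed association.** With both margins 25/25, the expected cell a satisfies (a/(25−a))² = OR. Here φ = (2a−25)/25 is both the share and the sex-risk correlation. With both terms in the model, the variance inflation is 1/(1−φ²).

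| Assumed OR | a | φ | Variance inflation |
|---|---|---|---|
| 1 | 12.5 | 0 | 1.00 |
| 2 | 14.6 | 0.17 | 1.03 |
| 4 | 16.7 | 0.33 | 1.125 |

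**5. Effect on the gender test.** Assume no true gender effect, a risk effect of 0.73 SD (step 1) and a normal approximation on subject means. Averaged over k, the false-positive rate is about 5.1%, 5.9%, 7.5% and 11.2% for odds ratios 1, 1.5, 2 and 3. Given an 18/7 split it is about 20%.

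**6. After a joint quota.** With 13/12 and 12/13, the share is (26−25)/25 = 0.04. Exact balance is impossible with 25 per risk group.

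**The case against.** The strongest reply is that the harm to the gender test comes mainly from the missing risk-group term in section 2.8.2. Adding that term would remove most of the confounding without any change to enrolment, and adjustment is an accepted alternative to balancing in an observational study. This largely stands, and the fix therefore includes the term. It does not make the quota pointless: the models as listed do not adjust, and adjustment leaves the precision loss of step 4. That loss is small at an odds ratio of 2 and 12.5% at 4.

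It can also be said that a journal article condenses the full protocol, which may hold a cell-level enrolment rule. That is possible. The article does, however, state the rule and attaches both ratios to the whole enrolled population.

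A reader might infer more than the documents support:

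- *That the risk-group comparison is biased.* This needs sex to affect the interdental flora, and no figure for that is given.
- *That the bias is systematic.* This needs sex and risk to be associated among those enrolled. If they are not, the imbalance is by chance, and over repeated studies the false-positive rate stays near 5%.
- *That a fixed number of bacteria out of the 1,300,000 would move into the gender effect.* The model uses log counts. The proportions carry over to that scale; absolute counts do not.
- *That extreme splits are likely.* They comply with the text, but by chance 17/8 or worse has probability 0.023.

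**Conclusion.** The point holds in a limited form. The stated ratios leave the sex-by-risk split open, and the listed models do not repair this: the gender test has no risk term and no sex adjustment is named for the risk-group regression. The share of a risk effect that can enter the gender coefficient is (2k−25)/25. Its absolute value is 20% or more with probability about 0.26 by chance alone, and its expected value is about 17% or 33% under assumed odds ratios of 2 or 4. The false-positive rates in step 5 also rest on an SD inferred from the sample-size statement and on an effect stated for raw counts, so they are illustrative. This is a cheap improvement to make before enrolment, not a flaw that invalidates the study.

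**What to change.** In section 2.3, replace the two marginal ratios with one joint quota: 13 male and 12 female in one risk group, 12 male and 13 female in the other, closing each cell when it is full. The total stays at 50 and both 1.0 ratios still hold.

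In section 2.8.2, include risk group together with gender as fixed effects in the mixed model.

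The cost is a sentence in each section and a four-cell enrolment log. The last cell may take longer to fill within the 2-month period. This is a real constraint: section 2.2 describes a mainly low-income population, and Table 1 lists low socioeconomic status as a high-risk factor, so low-risk subjects may be scarce. If the last cell cannot be filled, the model with both terms still removes most of the confounding.

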### Repartition of subjects according to caries risk conditions

2.4

The American Academy of Pediatric Dentistry [3] sets out criteria which will be used, with certain modifications, to classify patients according to their carious risk (Table 1). The low carious risk subjects presented Caries Protective Terms, i.e., brushing daily with fluoridated toothpaste and regular dental care, Caries Risk Indicators, i.e., socio-economic status (medium, high) and snacking (low, medium) and Clinical Indicators, i.e., less than one interproximal lesion and no enamel defects nor active white spot lesions and adequate saliva flow rate. The high carious risk subjects presented Caries Protective Terms, i.e., no daily brushing with fluoridated toothpaste and/or irregular dental care and/or Caries Risk Indicators, i.e., low socio-economic status and high snacking and/or Clinical Indicators, i.e., more than one interproximal lesion and/or active white spot lesions and/or enamel defects and/or inadequate saliva flow rate.

**Table 1 tbl1:** Adolescent caries risk assessment.

FACTORS	HIGH RISK	LOW RISK
Biological (interview)		
- Patient with low socioeconomic status	Yes	No
- Patient has >3 between meal sugar-containing snacks or beverages per day	Yes	No
Protective (interview)		
- Patient brushes teeth daily with fluoridated toothpaste	No	Yes
- Patient has regular dental care	No	Yes
Clinical Findings (International Caries Detection and Assessment System (ICDAS) and salivary tests)		
ICDAS		
- Patient has >1 interproximal lesion	Yes	No
- Patient has active white spot lesions or enamel defects	Yes	No
Salivary tests (hydration, salivary consistency, resting saliva pH, stimulated saliva flow, stimulated saliva pH and saliva buffering capacity)		
- Patient has high salivary risk	Yes	No

### Clinical examination

2.5

One trained and calibrated dentist who is experienced with the clinical indices will perform the clinical examination.

#### Dental examination

2.5.1

In reference to the International Caries Detection and Assessment System (ICDAS) criteria [14], adolescents will receive a clinical oral examination. After removing the dental plaque with a toothbrush or a professional prophylaxis, drying with gauze or air (5 s), the teeth will be observed under light (Orascoptic Endeavor headlamp system) without magnification and, a ball-end probe (WHO probe) could be used to determine the ICDAS score. This score will permit to determine the presence or absence of carious lesion (code 0: absence of carious lesion, code 1 to 6: carious lesion at different stages) [14]. There will be no radiography carried out. Adolescents will be informed of any conditions requiring treatment.

#### Salivary tests

2.5.2

This aims at investigating hydration, salivary consistency, resting saliva pH, stimulated saliva flow, stimulated saliva pH and saliva buffering capacity. All tests will be performed according to the instructions of the manufacturer (Saliva-Check Buffer test, GC France SAS, Sucy-en-Brie, France). All patients were refrained from eating, drinking, smoking, and performing oral hygiene procedures for 2 h before saliva collection. The tests will realized 30min after awakening at least, between 9:00 a.m. and 11:00 a.m [[15], [16], [17]]. The resting saliva consistency will be classified as sticky frothy or frothy bubbly or watery clear by observing the saliva in the floor of the mouth. The resting flow saliva will be evaluated by measuring the time to see new saliva droplets after drying the lip labial mucosa with a gauze (>60 s: low resting flow rate, 30–60 s: normal resting flow rate, < 30 s: high resting flow rate). The resting saliva pH will be measured with a pH strip (pH 5.0–5.8: highly acidic saliva, pH 6.0–6.8: moderately acidic saliva, pH 6.8–7.8: healthy saliva). The stimulated salivary flow rate will be analysed as the volume of saliva collected while the patient chewed a paraffin pellet for 5 min (<3.5 ml: very low, 3.5–5 ml: low, > 5 ml: normal). The salivary buffering capacity will be evaluated by depositing stimulated saliva on a test strip containing three different acid challenges.

### Interdental microbiota sample

2.6

Four interdental sites (15–16, 25–26, 35–36, and 45–46), free from caries (ICDAS code 0), will be assessed for each subject. The adapted interdental brush (Curaden, Kriens, Switzerland) will be determined by using a Curaprox IAP calibration probe (Curaden) [18]. Then, the isolation of each tooth selected for sampling will be performed by using sterile dental cotton rolls and a calibrated, sterile interdental brushes (IDB) will serve to remove the interdental biofilm. The IBDs containing the individual samples will be stored in sterile tubes at 4 °C for later laboratory treatment [19,20].

### Microbiological analysis

2.7

Quantification of the total number of bacteria and 26 pathogens will be performed by real-time PCR. The pathogens selected periodontal or carious bacteria: *Actinomyces odontolyticus, Aggregatibacter actinomycetemcomitans, Bifidobacterium dentium, Campylobacter rectus, Campylobacter gracilis, Capnocytophaga ochracea, Clostridium cluster IV, Clostridium cluster XIV, Eikenella corrodens, Fusobacterium nucleatum, Lactobacillus* spp.*, Parvimonas micra, Porphyromonas gingivalis, Prevotella intermedia, Prevotella nigrescens, Rothia dentocariosa, Scardovia wiggsiae, Streptococcus cristatus, Streptococcus mitis, Streptococcus mutans, Streptococcus salivarius, Streptococcus sanguinis, Streptococcus sobrinus, Tannerella forsythia, Treponema denticola,* and *Veillonella parvula.* Simplex quantitative real-time PCR assays will be performed in a volume of 10 μL (2 μL of DNA extract, 1 × SYBR® Premix Ex TaqTM Tli RNaseH Plus and 1 μM of each primer) (TaKaRa, Shiga, Japan).

